### Data management

Data will be collected using standardized paper-based forms and questionnaires according to standardized operating procedures. Data will be entered into a computer by trained data entry clerks, we will verify data by range and consistency checks, and data cleaning will be done weekly. Any discrepancies will be corrected by cross-checking against the corresponding original forms and subsequently amended in the final dataset.

All blood slides will be labelled with the patient’s unique ID number and date of collection to help ensure anonymity. To minimize any loss to follow-up, we will keep following up all residents and maintain their database, even if they move out of the trial area or move from one cluster to another cluster with a different intervention. For residents or respondents who are not present at the time of the visit by project staff, basic information about dates and reasons for absence will be sought from other community members such as friends or neighbors. The epidemiological data, economic evaluation data and entomological data will all be kept separately. All databases will be password protected and only accessed by research team and data entry clerks for data entry, cleaning and analysis. Furthermore, data will be stored for at least 5 years and be made publically available.

Each of the principal investigators of the epidemiological, economic evaluation and entomological studies will maintain records in compliance with Good Clinical Practice (GCP) for regulatory or institutional requirements. Authorized representatives from the funding agency, ethical committees or regulatory bodies may inspect all documents and records of the trial. The research team will explain any deviation from the originally approved protocol. Moreover, any deviation from the protocol that will have an impact on the conduct of the study will also be immediately reported to the funding agency and the local Institutional Review Board (IRB) as appropriate.

### Analytical plan

The primary health outcome measure is malaria incidence determined by the detection of *P. falciparum* or *P. vivax* using RDTs. All analyses will be conducted on an intention-to-treat basis, regardless of whether the individual household members use LLINs, IRS or not. Malaria cases diagnosed with an infection within 28 days of the first episode with the same *Plasmodium* species will be censored and will not be included in the analysis. An analysis will be performed as a community randomized trial with time-person as the denominator. All analyses will be conducted using Stata version 13 (StataCorp LP, College Station, TX, USA), and primary and secondary outcomes will be compared between the different intervention arms and control groups. The main outcome variable, malaria incidence based on PCD, is assumed to follow a Poisson distribution based on a random and independent occurrence. Hence, a generalized Poisson log linear model will be fitted to measure for associations between the outcome variable and predictors. The main outcome variable will also be analyzed as a binary variable and will be compared in the intervention and control clusters using multilevel mixed-effects logistic regression models, taking into account the clustering effects. In addition, we will also analyze the data using the population as the denominator (e.g., with a generalized estimating equation (GEE), multilevel analysis or spatial analysis) to help assess the effect of the intervention.

To control for potential confounding factors, the clustering effect of villages, the effect of repeated measurement in the same individual and individual level covariates (such as age, gender, LLINs’ use) will be taken into consideration during the analysis. Other potential confounding factors will also be adjusted for in the regression analysis, and all estimates will be presented with 95 % confidence intervals. Time will be included as a fixed effect that will allow any interaction with the interventions to be quantified.

The WHO age-adjusted cut-off for Hb will be used to classify anemia in children [71]. For children between 6–59 months of age, a normal Hb level is defined as Hb of 11.0 g/dl or greater and as mild at 10.0–10.9 g/dl. Moderate anemia is defined as children with an Hb level of 8.0–10.9 g/dl while severe anemia is defined as an Hb level of less than 8.0 g/dl. At a community level, a prevalence of anemia will be stated to be severe if over 40 % of the children are anemic (combining mild, moderate and severe) and moderate if the prevalence is 20–39.9 %. We will measure the weight and height of all children under the age of 5 years, and calculate the anthropometric indices such as weight for height, height for age, and weight for age. Both malaria and anemia prevalence data will be compared in the intervention and control clusters using multilevel mixed-effects logistic regression models, taking clustering effects into account.

Cost-effectiveness, expressed as an incremental cost-effectiveness ratio (ICER), will be calculated for each outcome and arm using standard DALY weights. The interventions will be ranked according to cost-effectiveness, whereas inequality in terms of health outcomes, will be measured by the Gini coefficient and the concentration index [72].

The agreement between the two mosquito collection methods, HLC and light traps, in assessing mosquito sampling efficiency will be calculated by a parametric approach based on an analysis of variance and simple graphical methods. Indoor and outdoor *Anopheles* densities will be compared among the study arms using a one-way analysis of variance (ANOVA) if data are normally distributed or using a Mann-Whitney *U* test if data are non-normally distributed.

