### Interventions

#### Long-lasting insecticidal nets (LLINs)

The LLINs distributed for this trial were PermaNet 2.0 rectangular, 100 denier, light blue, family size (160 cm width x 180 cm length x 150 cm height) purchased in June 2014 from the Vestergaard Frandsen Group SA (Vestergaard Frandsen, Lausanne, Switzerland). The PermaNet 2.0 net is a factory-treated mosquito net manufactured with deltamethrin, which is expected to retain its biological efficacy for a minimum of 20 standard WHO washes or approximately 3 years under field conditions [53].

The *MalTrials* project bought a total of 10,000 PermaNet 2.0 LLINs for this trial. The nets were imported and arrived in the study site on 16 September 2014, and distributed to study households from 1 to 5 October 2014. All households in the LLINs + IRS and LLINs alone arms received new LLINs free of charge at the beginning of the intervention regardless of the previous ownership, with householders maintaining their existing nets at the time of distribution. The number of new LLINs distributed to each household was based on the household size recommended by the national malaria guidelines [43], i.e., one net for a family of 1–2, two nets for a family of 3–5, three nets for a family of 6–7 and four nets for a family of 8 or more people.

In advance of the LLINs distribution, all village residents were made aware of the distribution of the nets through house-to-house visits, village leaders and community elders. The net distribution was done in the center of the village based on a pre-determined registration list of households in each village by the *MalTrials* project personnel in collaboration with the district and village health workers. Households who did not receive the nets during the distribution schedule were identified and received their nets later. Education about, and a demonstration of how to use, LLINs were given to the recipients by trained field staff and selected village residents.

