#### Epidemiological data collections

PCD of malaria cases at the health posts will be carried out throughout the trial using RDTs, and thin and thick blood smears for microscopic examination. We will recruit 24 data collectors (two data collectors per *kebele*) for a weekly household visit, 14 nurses (one nurse per *kebele*) for malaria diagnosis and treatment at the health posts and three field supervisors. Data collectors will be trained on questionnaire specifics, interviewing techniques and household visits. They will visit households weekly to help identify residents with fever, or a history of fever in the last 48 hours, to refer to the health posts and track information on LLINs’ use by household members during the night before the survey.

The research team and supervisors will make regular field visits for quality control of the work done at health posts. Each field supervisor will be responsible for 59 clusters, and will meet with data collectors and health workers at the health posts at least once a week. During these visits supervisors will check patient registration books, malaria surveillance forms and the availability of antimalarial commodities, and collect completed forms and blood slides and bring them back to the project’s office. Throughout the study period, all health posts that participate in the trial will be provided with multispecies and mixed infection-detecting RDTs, artemether-lumefantrine (AL) and chloroquine obtained from the Oromia Regional Health Bureau (ORHB). The RDT that will be provided is the CareStart® Malaria *Pf/Pv* combo test (Access Bio, Inc., Somerset, NJ, USA), which is individually packaged with an alcohol swab, lancet, capillary tube, buffer and test device.

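### Net use recorded during follow-up is listed as a confounder to adjust for, which would remove all or part of the LLIN effect in contrasts that differ by LLIN allocation

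*Protocol article*

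**What the plan says.** The Analytical plan opens with the analysis principle: "All analyses will be conducted on an intention-to-treat basis, regardless of whether the individual household members use LLINs, IRS or not". Its second paragraph sets out the adjustment. It begins "To control for potential confounding factors, the clustering effect of villages", adds repeated measurement in the same person, and ends with "individual level covariates (such as age, gender, LLINs’ use", all to be taken into account in the analysis. The next sentence is "Other potential confounding factors will also be adjusted for in the regression analysis".

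How net use is measured is stated elsewhere. Under Epidemiological data collections, the weekly household visitors "track information on LLINs’ use by household members during the night before the survey". The section on LLINs also describes use and retention as monitored at the weekly visit. On allocation, "All households in the LLINs + IRS and LLINs alone arms received new LLINs free of charge at the beginning of the intervention". Households kept the nets they already had.

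The timetable (Table 1) puts randomisation of clusters in June 2014 and the start of weekly visits in September 2014. The LLIN section dates net distribution to 1 to 5 October 2014.

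**The concern.** A confounder in a randomised comparison would have to be a cause, or a marker of a cause, that precedes allocation. Net use during follow-up does not qualify. It results from being given nets, and it is a main route by which a net protects the person under it, so it is a mediator of the LLIN intervention. A model containing both arm and use no longer estimates the effect of allocation. It estimates what remains of that effect once use is held fixed.

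The primary objective compares LLINs + IRS with LLINs alone and with IRS alone. In the second of these, nets are the only randomised difference. The comparisons of LLINs alone with control and with IRS alone, named in the Background, also differ by LLIN allocation.

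The adjusted model would fit without warning. Because old nets were kept, and because Trial oversight says that controls may obtain nets elsewhere, use will vary within every arm and will not coincide with arm. The estimates also feed the economic evaluation, which takes its effectiveness parameters from this trial.

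**Working it through.** **Timing.** All weekly records follow randomisation in June 2014. Apart from at most the first few weeks, they also follow net distribution in October 2014. The covariate is therefore a post-allocation one.

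**The plan's own sample size.** Inputs from the Sample size section: comparator rate λ0 = 7.85 per 10,000 person-weeks, k = 0.27, 175 people × 116 weeks = 20,300 person-weeks per cluster (y), 25% reduction (λ1 = 5.8875 per 10,000), two-sided 5%, 90% power.

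c = 1 + (1.960 + 1.282)² × [(λ0 + λ1)/y + k²(λ0² + λ1²)] / (λ0 − λ1)²

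= 1 + 10.51 × (6.77×10⁻⁸ + 7.02×10⁻⁸) / 3.85×10⁻⁸ = 38.6, so 39 clusters per arm.

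The stated 44 is larger and gives 93.4% power. An unstated 20% loss of person-time would give 43.2, so 44. The difference is on the conservative side and does not affect this point. The formula is used below only to scale the consequence.

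**Contrast differing by LLIN allocation.** Assume a true total rate ratio of 0.75, a proportion u1 using nets in the LLIN arm and u0 in the comparator, and a user versus non-user rate ratio θ.

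- Whole effect through use: (1 − u1 + u1θ)/(1 − u0 + u0θ) = 0.75. With u1 = 0.80 and u0 = 0.10, θ = 0.475/0.725 = 0.655. Check: 0.724/0.9655 = 0.75. Holding use fixed leaves a ratio of 1.00.
- Half the effect (on the log scale) through use: the part not through use is √0.75 = 0.866, and that is what remains after adjustment.

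Simulation agreed with this. Each scenario had 100 trials, 44 clusters per arm, gamma cluster effects with k = 0.27, and a Poisson model with a person-time offset, fitted with and without use.

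| Use, LLIN arm / comparator (assumed) | Unadjusted, all through use | Adjusted, all through use | Unadjusted, half through use | Adjusted, half through use |
|---|---|---|---|---|
| 65% / 0% | 0.75 | 1.01 | 0.74 | 0.85 |
| 65% / 20% | 0.75 | 1.00 | 0.75 | 0.87 |
| 80% / 10% | 0.75 | 1.00 | 0.74 | 0.85 |
| 90% / 30% | 0.76 | 1.01 | 0.75 | 0.87 |

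The use levels hardly move the adjusted ratio. The mediated share does. Put through the formula above with 44 clusters, a ratio of 0.75 has 93% power, 0.866 has 43%, and 1.00 has only the 5% error rate. These power figures are rough, because the formula takes no account of the precision of the adjusted model.

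**LLINs + IRS versus LLINs alone.** Assume an IRS rate ratio of 0.75 at fixed use, θ = 0.6, and 65% use with LLINs alone.

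- Equal use: simulated 0.74 with and without adjustment.
- Use of 55% or 45% in the combined arm: unadjusted (intention-to-treat) 0.80 or 0.84, adjusted about 0.76. Adjustment makes the combination look better.
- Use of 75% in the combined arm, by arithmetic: intention-to-treat 0.75 × (1 − 0.4×0.75)/(1 − 0.4×0.65) = 0.75 × 0.70/0.74 = 0.71, against 0.75 at fixed use. Adjustment makes it look worse.

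**The case against.** The strongest reply is that the text does not say that the primary model adjusts for net use. The covariates are to be considered during analysis. No model is named, several are described, and the same sentence covers clustering and repeated measures. An unadjusted arm comparison with a supportive adjusted model would be compatible with the wording. This stands as a limit on certainty. It does not remove the problem: the stated purpose is control of confounding, and the following sentence says that other confounders will also enter the regression, so adjustment is the natural reading. No sentence reserves net use for a supportive model or restricts it to baseline.

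A reader might infer that the two statements are logically incompatible. That goes too far. Everyone can be kept in the assigned arm while a covariate is added. What changes is the quantity estimated, which is then no longer the effect of allocation regardless of use.

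A reader might also infer that the whole effect is adjusted away. That follows only if all of it acts through personal use and any used net protects equally. Whole villages were given nets, so a community-wide effect may exist, and new nets may protect more than the older ones that households kept. Either would survive adjustment.

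Finally, a reader might multiply the Background's national figures, 55% ownership and 65% use by children under 5 in owning households, to get 36% background use. Those figures do not describe all ages in this district, and nothing above rests on them.

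**Conclusion.** The point holds, with limits. A post-randomisation consequence of LLIN allocation is named as a confounder for the incidence analysis, at odds with the intention-to-treat statement in the same section.

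In contrasts that differ by LLIN allocation (the primary contrast LLINs + IRS versus IRS alone, and also LLINs alone versus control or versus IRS alone), adjustment would remove all or part of the LLIN effect. From an assumed true ratio of 0.75, the adjusted ratio is about 0.85 to 0.87 with half the effect through personal use and about 1.00 with all of it. The use levels, the mediated share and the true ratio are assumptions. Unmeasured causes shared by net use and malaria were not modelled and could add further bias.

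The documents do not support extending this to the other primary contrast as a loss of effect. LLINs + IRS and LLINs alone have the same net allocation, so the IRS effect stays in the model. The estimate moves away from the intention-to-treat effect only if spraying changes net use, and then in either direction.

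**What to change.** Delete follow-up LLIN use from the covariates of the primary and secondary effect models. State that adjustment is limited to baseline variables: age, sex, cluster-level baseline factors and, if wanted, net use before distribution. Since Table 1 places baseline data collection (July to August 2014) after randomisation (June 2014), pre-distribution net use should be used only if it was recorded before villages knew their allocation. Report follow-up net use by arm as a descriptive process measure, or in a separately labelled per-protocol or mediation analysis.

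The cost is about one sentence in the analysis plan. No new data and no change of design are needed, and the weekly net-use records keep their value for the descriptive and labelled analyses.

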At the end of the main malaria transmission season each year, the Hb concentration will be assessed in children 6–59 months old for assessing the prevalence of anemia using a portable photometer (HaemoCue®, Ångelholm, Sweden) in the field. Through house-to-house visits, a single finger-prick sample will be taken from each child, and children’s height and weight will also be measured. A Hb cut-off point of less than 11.0 g/dl will be used to decide whether a child has anemia, and will be further classified into mild, moderate and severe anemia.

Community-based malaria prevalence surveys will be conducted on a representative sample of households from each arm of the trial during the main transmission season (September to November) each year among all age groups. All household members will be eligible to be included in the study. Allowing for ineligible households, absence on the day of the survey and refusals at the household and individual level, approximately 5500 individuals from 1100 households will be estimated to be included in the study. This would provide an average 275 households from each arm of the trial to be included in the study. The households will be randomly selected from the total list of households in all arms of the trial. The heads of the households or their representatives will be interviewed using a pre-tested structured questionnaire. Voluntary individuals will be tested for malaria parasites using RDTs. Moreover, blood slides will also be collected for microscopic examination.

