#### Economic evaluation data collections

Costing will be done based on the cost of the interventions from a health systems perspective, with cost data collected by interviewing individual malaria patients, family members and the DHO personnel. The main cost outcome measure will be the total costs of interventions, including all resources used to deliver the interventions and recurrent costs such as personnel, supplies and materials, the operation and maintenance of buildings, utilities and communication costs, in addition to capital costs such as buildings, equipment, and vehicles. The costing of the intervention will be done from the provider’s perspective using a standard malaria costing tool developed by the WHO [57]. The economic evaluation of health outcomes will be evaluated by the number of malaria cases averted and DALYs gained as a result of the interventions using incidence data. The number of deaths averted due to the interventions will be calculated based on the case fatality rates of malaria.

Economic evaluation, cost-effectiveness/utility analysis, presenting cost per malaria case prevented and costs per DALY averted will all be employed. The DALYs will incorporate both morbidity estimates from malaria episodes and anemia among children. We will develop a Markov life cycle model to account for the recurrent nature of malaria disease, with a varying amount of risk for repeated episodes during different seasons of the year. The cost of illness study will be conducted in the same district from non-trial villages to account for saved disease treatment costs. Epidemiological and effectiveness parameters will be based on the findings of this research project, while the clinical course of the diseases will be based on a review of the best available literature. Standard DALY weights will be utilized. Moreover, this trial will incorporate an evaluation of the distributional impact of the interventions using inequality analysis techniques and a decomposition of the inequality into various socioeconomic factors using an extended cost-effectiveness analysis (ECEA). In the ECEA, we will estimate the benefit of the interventions across different levels of income group in terms of the number of deaths prevented, the net financial risk protection provided, the out-of-pocket expenditure averted and the number of poverty cases prevented.

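### The haemoglobin bands for mild and moderate anaemia overlap, so every child in the mild band also meets the definition of moderate anaemia

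*Protocol article*

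**What the plan says.** The relevant text is in four parts of the protocol article.

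- **Epidemiological data collections** sets the threshold for any anaemia: "A Hb cut-off point of less than 11.0 g/dl will be used to decide whether a child has anemia". Anaemia "will be further classified into mild, moderate and severe anemia".
- **Analytical plan** refers to WHO age-adjusted cut-offs and gives the bands for children aged 6–59 months. For the top of the scale, "a normal Hb level is defined as Hb of 11.0 g/dl or greater and as mild at 10.0–10.9 g/dl". The next sentence says "Moderate anemia is defined as children with an Hb level of 8.0–10.9 g/dl", and "severe anemia is defined as an Hb level of less than 8.0 g/dl". At community level, the prevalence of anaemia is called "severe if over 40 % of the children are anemic (combining mild, moderate and severe"), and moderate at 20–39.9 %. Anaemia prevalence is to be compared between arms by mixed-effects logistic regression.
- **Study endpoints** makes mean Hb the secondary health outcome.
- **Economic evaluation data collections** says "The DALYs will incorporate both morbidity estimates from malaria episodes and anemia among children", with standard weights.

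**The concern.** A classification into three grades should give each anaemic child one grade. Here the mild and moderate bands share the upper limit 10.9 g/dl, so a child with Hb 10.5 g/dl is both mild and moderate. Two analysts following the text could produce different severity tables from the same data: one might count such children in both classes, and the other might pick one class by an unstated rule.

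Reducing anaemia in children under 5 years is one of the trial's secondary objectives. If severity is reported by arm with these bands, a difference in moderate anaemia would mix two grades under one label. Under the illustrations below, most of the children so labelled would be mild cases. If the economic evaluation weights anaemia by grade, the same children would have no determinate weight.

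**Working it through.** **Inputs from the protocol (Analytical plan; Epidemiological data collections), in g/dl.** Normal is 11.0 or more, mild 10.0–10.9, moderate 8.0–10.9, severe below 8.0, any anaemia below 11.0. There is no sample size or power figure to reproduce; the check is on the bands themselves.

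**Step 1: overlap and gaps.** The limits are stated to one decimal, so I listed Hb in steps of 0.1 from 4.0 to 15.9.

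- Mild holds 10 values (10.0 to 10.9) and moderate holds 30 (8.0 to 10.9). All 10 mild values are among the 30 moderate ones.
- Severe and moderate do not overlap, and no value is left unclassified.
- The union of mild, moderate and severe is exactly Hb below 11.0.

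The only conflict is therefore between mild and moderate. Any-anaemia prevalence, counted once per child, does not depend on it.

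**Step 2: size, under assumptions.** The protocol gives no Hb distribution. I assumed a normal distribution with mean 11.0, 11.5 or 12.0 and SD 1.2 or 1.5 g/dl, with values rounded to 0.1. With F the normal distribution function:

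- mild = F(10.95) − F(9.95)
- moderate as written = F(10.95) − F(7.95)
- moderate excluding the stated mild band = F(9.95) − F(7.95)
- severe = F(7.95)
- any anaemia = F(10.95)

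Worked case, mean 11.5 and SD 1.5: F(10.95) = 0.357, F(9.95) = 0.151, F(7.95) = 0.009. Mild = 0.357 − 0.151 = 0.206. Moderate as written = 0.357 − 0.009 = 0.348. Moderate excluding mild = 0.151 − 0.009 = 0.142. Adding the three classes as written gives 0.206 + 0.348 + 0.009 = 0.563, against 0.357 for any anaemia, a ratio of 1.58.

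| Mean, SD | Mild | Moderate as written | Moderate excluding mild | Any anaemia | Mild share of moderate as written | Sum of classes / any anaemia |
|---|---|---|---|---|---|---|
| 11.0, 1.2 | 0.293 | 0.478 | 0.185 | 0.483 | 0.61 | 1.61 |
| 11.0, 1.5 | 0.245 | 0.466 | 0.221 | 0.487 | 0.53 | 1.50 |
| 11.5, 1.2 | 0.225 | 0.322 | 0.097 | 0.323 | 0.70 | 1.70 |
| 11.5, 1.5 | 0.206 | 0.348 | 0.142 | 0.357 | 0.59 | 1.58 |
| 12.0, 1.2 | 0.147 | 0.190 | 0.043 | 0.191 | 0.77 | 1.77 |
| 12.0, 1.5 | 0.156 | 0.238 | 0.082 | 0.242 | 0.65 | 1.65 |

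The ratio of moderate as written to moderate excluding mild runs from 0.466/0.221 = 2.1 to 0.190/0.043 = 4.4. The last column matters only if someone adds the three class prevalences.

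**Step 3: what uses the bands.** Malaria incidence does not involve Hb. Mean Hb uses no bands. Any anaemia has its own threshold of 11.0. The community thresholds of 20 % and 40 % use the share of children with any grade, which Step 1 shows is unchanged. What remains is the severity classification itself, and anything built on it.

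**The case against.** The strongest reply is that little in the stated analysis depends on these bands. The protocol names no severity-specific comparison between arms: the secondary health outcome is mean Hb, and the planned model is for anaemia prevalence. The shared 10.9 may be a typing slip, and the authors cite the source against which it can be corrected. Even read literally, the proportion of children with Hb 8.0–10.9 g/dl is well defined and can be compared between randomised arms.

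Most of this stands, and it limits the consequence. It does not remove the contradiction. The protocol commits to classifying anaemic children by grade and prints exact limits that cannot serve that purpose. It also does not settle which limit is the slip.

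Three stronger readings are tempting, and the documents do not support them.

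- A reader might infer that anaemia DALYs are double counted and the cost-effectiveness ratios distorted. The protocol says only that childhood anaemia enters the DALYs with standard weights. It does not say that anaemia enters by grade, that these bands drive the weights, or that class counts are added.
- A reader might infer that severity comparisons are uninterpretable. They would be mislabelled, which is a lesser fault.
- A reader might suspect the severe limit as well, on the ground that the bands come from different parts of the WHO source. That source is not at hand, and within the protocol the severe band meets the moderate band at 8.0 with neither overlap nor gap.

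**Conclusion.** The point holds as a contradiction in a stated analysis definition. The mild band lies wholly inside the moderate band, which conflicts with the intended three-way classification. This needs no assumption; it follows from the printed limits.

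The size does rest on assumptions. Over the six normal distributions tried, moderate anaemia is about 19–48 % of children as written and 4–22 % once the stated mild band is excluded, and 53–77 % of children labelled moderate are also mild. The protocol supplies no Hb mean or SD, so this range is an illustration, and no single value from it should be quoted alone.

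The effect is confined to severity-specific anaemia results, and to DALYs and cost-effectiveness ratios only on the unstated condition that they use these classes. It is worth correcting because the classification is planned and the correction is nearly free, but it does not threaten the trial's main conclusions.

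**What to change.** Reconcile the mild and moderate limits in the Analytical plan with the cut-offs cited there, so that the grades are mutually exclusive and mild, moderate and severe together cover exactly Hb below 11.0 g/dl. The cited source should decide which limit changes; the protocol's text cannot. State that the same grades apply to any severity-specific comparison between arms, and to the DALY calculation if anaemia is weighted by severity there.

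The cost is one corrected definition and a cross-reference in the economic section. Hb is measured as a concentration in each child, so children can be reclassified from recorded values. No data collection, sample size or primary analysis changes.
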